### Statistical analyses

All analyses will be based on the initial treatment assignment (intention-to-treat). Missing data will be treated according to the recommendations of Hair *et al*. [58]. First, the extent of missing data will be determined; then, the level of randomness (missing at random, missing completely at random or missing not at random) will be diagnosed applying Little’s missing completely at random test and t-tests for independent variables. According to Cho and Leonhart [59], data missing completely at random is very unlikely in a rehabilitation research setting, so missing data will probably be imputed with a missing at random-capable method (for example, using multiple imputations).

We plan to use a between-group analyses of covariance (ANCOVA) with baseline scores of the outcome variables as covariates to adjust for baseline differences. With these, we compare differences in the main outcomes between the intervention and control group at post-treatment (T_2_) and follow-up (T_3_) time points. Alpha levels will be adjusted for multiple testing. Cohen’s *d* will be calculated to measure the effect sizes. All statistical analyses will be performed using IBM SPSS Statistics 20. If we fail to achieve the target sample size within the given time frame and resources of our study, we will use analyses of variance (ANOVA) instead. Due to randomization, group differences at baseline (T_1_) will be not likely. We will then test for an interaction effect between group and time from T_1_ to T_2_ and a main effect of group from T_2_ to T_3_.

Explorative analyses will be conducted to examine potential effect moderators (demographic variables and coping style, such as seeking social integration or seeking information). Interaction terms of potential moderator variables and treatment will be created and analyzed by linear regression.

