### Outcome measures

#### Procedure of assessments

The control group will receive all questionnaires by mail. The intervention group will receive the questionnaires at baseline and at 18-week follow-up, also by mail; the questionnaires at post-treatment will be handed out together with a short group evaluation questionnaire in the last group session. For returning the questionnaires, participants will be provided with stamped and addressed envelopes. The session questionnaires for the process evaluation of the group program will be handed out after each session, and patients will be asked to complete and return them immediately after the group session.

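### The plan says it will diagnose MAR, MCAR or MNAR with Little's test and t-tests, which cannot separate MAR from MNAR, and it leaves the missing-data method open until after that step

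*Protocol article*

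**What the plan says.** The Statistical analyses section sets out an order of work: "First, the extent of missing data will be determined; then, the level of randomness" is to be examined. The aim of that second step is a three-way classification ("the level of randomness (missing at random, missing completely at random or missing not at random) will be diagnosed applying"). The tools named for it are Little's MCAR test and t-tests.

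The handling method comes after this. Citing an outside source, the section holds that "data missing completely at random is very unlikely in a rehabilitation research setting" and concludes that "missing data will probably be imputed with a missing at random-capable method", with multiple imputation as an example. The outcome model is a "between-group analyses of covariance (ANCOVA) with baseline scores of the outcome variables as covariates", at T2 and at T3.

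Under Procedure of assessments, the control arm receives every questionnaire by mail. The intervention arm receives its T1 and T3 questionnaires by mail, but its T2 questionnaire is handed out "in the last group session". The Discussion expects rather high response rates, accepts that some data will be missing and may cause bias, and relies on the same cited recommendations to limit it. No expected missing rate is given.

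**The concern.** MAR and MNAR differ in whether, given the observed data, missingness still depends on the values that were not observed. A test built only on observed data carries no information on that. Little's test and t-tests comparing patients with and without data on recorded variables address one question: is there evidence against MCAR? The section therefore promises a result that its tools cannot deliver.

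Two consequences follow. A rejection does not say whether MAR or MNAR holds. A non-rejection does not show MCAR, since the test may simply lack power. Because the method is described only as probable, and after this step, it can also be settled after the data have been seen.

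This matters more here than in a trial with identical data collection in both arms. T2 collection in one arm is linked to being present at the eighth session. Patients who stop attending could be the ones who do not return the T2 HADS-D, and they may be doing worse. At stake is the baseline-adjusted group difference on the primary outcome.

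**Working it through.** **Inputs from the protocol article.** f = 0.25, total N = 128, power 0.80, alpha 0.05 (Sample size calculation); 1:1 allocation (Assessment of eligibility and randomization); ANCOVA with baseline as covariate (Statistical analyses). For two equal groups d = 2f = 2 × 0.25 = 0.5.

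**The plan's own figure.** For an ANCOVA F test with 1 and 128 − 3 = 125 degrees of freedom, the noncentrality is N × f² = 128 × 0.0625 = 8.0 and the power is 0.801. The smallest N that reaches 0.80 is 128. The stated sample size reproduces and is not in dispute.

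**What the tests can show.** A simulation used N = 128, 1:1 allocation and a true adjusted effect of −0.50 SD (negative favours the intervention), with 4000 trials per mechanism. Three inputs are assumptions: about 20% of outcomes missing, a baseline-outcome correlation of 0.5, and a log-odds slope for missingness of 1 per SD. Each trial had one baseline and one outcome score. The tests were Little's test and a t-test of baseline by missingness, both at 5%. The estimate is the ANCOVA on observed cases.

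| Missingness mechanism | Little's test rejects | t-test rejects | Mean estimate |
|---|---|---|---|
| MCAR | 5.8% | 5.4% | −0.50 |
| MAR, driven by baseline | 98.5% | 98.1% | −0.50 |
| MNAR, unobserved part of outcome, opposite direction by arm | 4.9% | 4.5% | −0.80 |
| MNAR, outcome, intervention arm only | 18.6% | 17.8% | −0.64 |
| MNAR, outcome, same in both arms | 49.7% | 48.9% | −0.50 |

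The rejection rate does not track the bias. The tests rejected almost always under MAR, where the estimate was right. They rejected at about the nominal 5% in the MNAR case with the largest error (0.80 − 0.50 = 0.30 SD). Under intervention-arm-only MNAR they stayed silent in about four trials of five, with an error of 0.64 − 0.50 = 0.14 SD. A real data set has more variables, so these rates would change; the failure to separate MAR from MNAR would not.

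**Illustrative size of bias.** If a proportion p of an arm is missing and those patients are truly δ worse than MAR predicts, that arm's mean is too favourable by p × δ. The error in the difference is p × δ in the intervention arm minus p × δ in the control arm. Assume δ = 0.5 SD in the intervention arm and 0 in controls:

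- p = 0.10: 0.10 × 0.5 = 0.05 SD, and 0.05 / 0.5 = 10% of the planned d.
- p = 0.30: 0.30 × 0.5 = 0.15 SD, and 0.15 / 0.5 = 30% of the planned d.

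With the same p and δ in both arms the error is zero.

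**The case against.** The strongest reply is that the section does not make the tests a decision rule. Its stated reason for a MAR-capable method is a cited prior view that MCAR is very unlikely, not a test result. The only method named, multiple imputation, is also valid under MCAR, so a non-significant test need not lead to anything worse. This stands. A reader might infer that the test result selects the method, but no sentence says so, and any such rule in the cited recommendations cannot be seen here. What remains is that the method is only probable and follows the diagnosis, so it is not fixed.

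Other stronger readings also go beyond the text:

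- *A passed test would lead to complete-case analysis or single imputation.* Neither is mentioned. The wording does not exclude them, and no more can be said.
- *A MAR analysis would be reported as if MNAR had been ruled out.* Nothing states this, and the Discussion acknowledges bias from missing data.
- *The tests can never react to MNAR.* They rejected in 18.6% and 49.7% of trials in two of the simulated cases. They can flag a departure from MCAR but cannot attribute it to MNAR.
- *The lack of an MNAR sensitivity analysis is itself an error.* A condensed article may leave that to the full protocol or analysis plan, so it is not held against the plan.

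It is also fair to say that attendance is documented by the therapist. Used in the imputation, it would make MAR more plausible for patients who stop coming. That is an argument for fixing the imputation model, and it is part of the fix.

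None of this rescues the classification itself. It is a stated procedure that cannot work as described, and a separate analysis plan would not make that sentence correct.

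**Conclusion.** The point holds in limited form. The claim to diagnose MAR, MCAR or MNAR with Little's test and t-tests is wrong as stated, because these tools can at most give evidence against MCAR. The primary missing-data method is not fixed before that step, so the choice is open to the data. The different T2 delivery in the two arms makes missingness that differs by arm and relates to attendance a practical risk.

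The size for this trial is unknown, because no missing rate is given. The 0.05 to 0.15 SD range rests wholly on assumed inputs: 10 to 30% missing, a 0.5 SD shortfall, and no matching shift in controls. It shows one unfavourable case and is not an estimate. The logical point depends on none of these numbers. The sample size and the ANCOVA model are unaffected. The correction is worth making before analysis, but the flaw does not undermine the design.

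**What to change.** 1. Delete the statement that the mechanism will be diagnosed as MAR, MCAR or MNAR. Keep Little's test and the t-tests, if wanted, as a description of who has missing data.
2. Name multiple imputation under MAR as the primary method, whatever the tests show. Impute separately by arm, using baseline HADS-D, the scores at the other time points and, in the intervention arm, the documented attendance.
3. Add a delta-adjusted sensitivity analysis for MNAR: worsen the imputed intervention-arm HADS-D scores in steps until significance is lost, and report that tipping point.

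The cost is a change of wording and a little more analysis work. Sample size, assessments and conduct stay as they are. The Trial status section reports recruitment as unfinished in May 2015, so on that information the change could still be made before analysis.

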## Methods/Design

### Study design

This is a randomized, wait-list controlled trial. Study participants allocated at random to the intervention group will participate in the CBT group program for patients with somatic diseases and depressive or adjustment disorders immediately after contacting the clinic. Study participants allocated at random to the wait-list control group will follow the usual waiting process of our outpatient clinic. After completion of the follow-up assessment (about five months after randomization), study participants of the wait-list control group are also offered to participate in the group program. The three measurement points are scheduled for all study participants at baseline (immediately before initial consultation, T_1_), 10 weeks after randomization (post-treatment, T_2_) and 18 weeks after randomization (follow-up, T_3_). The 18-week follow-up measurement is scheduled in a relatively short interval of two months after treatment because we did not want to extend the usual waiting period of four months for individual psychotherapy for patients in the wait-list control group. For an overview of the study design see Fig. 1.

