#### Intervention design

The STEpS group program consists of eight weekly sessions of 100 minutes. The group size will be limited to eight patients and the group setting will be half-open: entry for new members will be possible with every new topic (every other session). The group program will be performed by a psychotherapist trained in CBT with experience in group psychotherapy. Before joining the group, new group members will have a short consultation with the group therapist for about 20 minutes. This consultation serves to get to know each other, to reduce any fears, to clarify any questions and to inform the new patient about the topics and procedures of the group program and the group rules (for example listening to each other and letting the other person finish talking). Patients will also receive a folder with an overview of the group topics, the group rules and enough space for their work sheets and individual notes. Furthermore, all patients will give their written consent that they will treat all information provided by other group members confidentially. The group sessions will take place at the outpatient clinic of the Institute for Psychology at the Albert-Ludwigs-University of Freiburg. During the sessions, tea and water will be offered and a short break of 10 minutes will be included.

The STEpS group program covers the following topics: behavioral activation (two sessions), cognitive restructuring (two sessions), coping with illness, social support, self-esteem and meaning. Every session will start with an exercise of progressive muscle relaxation as described by Jacobson [40], and with everybody giving a short summary of his or her current situation. Mindfulness-based exercises (for example, leaves on a stream) will be used as a break or closing exercise, but will not be a regular feature of the group program. All sessions will end with a final round (‘How do you feel at this moment? What is your personal take home message?’). For a detailed session overview see Table 1.

**Table 1 Tab1:** Overview of the STEpS group program

Session	Topic	Content
1	Behavioral activation I	- Psycho-education about the relationship between behavior and emotion: explanation of the downward mood spiral [60]
		- Selection of individual positive activities from a checklist [61] and rating of the selected activities
		- Scheduling three positive activities for the next week
2	Behavioral activation II	- Review of homework

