##### Psychotherapeutic process

For the evaluation of the therapeutic process in the group program patients evaluate each group session with a session questionnaire. The session questionnaire used is a modified version of the patient version of the Bern Post Session Report (BPSR 2000) [53], extended by group specific aspects. The Bern Post Session Report modified for groups (BPSR-G 2000) includes 26 items rated on a seven-point scale ranging from −3 (not at all) to +3 (exactly). The 11 scales cover session impacts (experiences of mastery, clarification, control, problem actualization and self-esteem), other common factors (therapeutic alliance and therapeutic progress), group specific factors (cohesion and alliance with group members) and global evaluation scales (session evaluation and group setting evaluation). The psychometric properties of the original BPSR 2000 are well established [53].

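### The planned ANCOVA, its ANOVA fallback and the sample size of 128 make no allowance for outcomes correlating within therapy groups, which exist in the intervention arm only

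*Protocol article*

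**What the plan says.** The main comparison is set out in the protocol article under Statistical analyses: "We plan to use a between-group analyses of covariance (ANCOVA) with baseline scores of the outcome variables as covariates". With this model, "we compare differences in the main outcomes between the intervention and control group at post-treatment" and again at follow-up. If recruitment falls short, "we will use analyses of variance (ANOVA) instead". Neither model has a term for the therapy group.

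Under Intervention design, "The group size will be limited to eight patients and the group setting will be half-open", and "entry for new members will be possible with every new topic (every other session" of the eight weekly sessions. On staffing: "The group program will be performed by a psychotherapist trained in CBT with experience in group psychotherapy". Under Intervention development, one reason given for keeping groups small or medium is to promote exchange and mutual support between patients.

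The other arm has no such structure. Under Study design: "Study participants allocated at random to the wait-list control group will follow the usual waiting process of our outpatient clinic". Randomization is individual, 1:1, to condition only.

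The Sample size calculation section gives 128 participants for f = 0.25, alpha 0.05 and power 0.8, adjusting for baseline severity. It mentions neither an ICC nor a design effect. Clustering is not among the limitations listed in the Discussion.

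**The concern.** This is a partially nested design: patients are randomized one by one, but one arm is then treated in shared groups. Patients who attend the same sessions with the same fellow members may end up more alike than patients from different groups, and this program is meant to work partly through interaction between members. An ordinary ANCOVA or ANOVA assumes independent residuals in both arms. If there is positive correlation within groups, it understates the variance of the intervention mean and hence of the group difference.

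P-values would then be too small and confidence intervals too narrow for the comparison that decides whether the program is put forward as a first-line option. The planned alpha adjustment does not help, because it deals with the number of tests and not with dependence between patients.

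**Working it through.** **Inputs from the protocol article.** f = 0.25, alpha 0.05, power 0.80, N = 128 (Sample size calculation); 1:1 allocation, hence 64 per arm (Assessment of eligibility and randomization); at most eight per group, entry every second session (Intervention design).

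**Assumed.** ICC 0.01 to 0.10, since none is given; m trial patients per group, with m = 8 (the ceiling) and m = 4; equal total variance in both arms; two-sided test; all 64 per arm analysed.

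**Step 1, the plan's own figure.** For two equal arms f = 0.25 is d = 0.5. A noncentral F test with 1 numerator degree of freedom, one covariate and noncentrality f² × N reaches 0.80 first at N = 128 (power 0.801). The same N results without a covariate. The figure is therefore reproduced under independence and contains no allowance for clustering.

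**Step 2, variance.** Design effect in the intervention arm: DE = 1 + (m − 1) × ICC. The control arm is unchanged, so the variance of the difference is multiplied by V = (1 + DE)/2. Example, m = 8 and ICC 0.05: DE = 1 + 7 × 0.05 = 1.35; V = 2.35/2 = 1.175; true SE / ANCOVA SE = √1.175 = 1.084.

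**Step 3, type I error of the planned test.** 2 × [1 − Φ(1.96/√V)].

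**Step 4, power of a valid test at N = 128.** Φ(0.5/√(2V/64) − 1.96) = Φ(2.83/√V − 1.96). This takes f = 0.25 as the effect on the baseline-adjusted scale. Without clustering the normal approximation gives 0.81.

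| m | ICC | DE | V | Type I error | Power |
|---|---|---|---|---|---|
| 8 | 0.01 | 1.07 | 1.035 | 5.4% | 0.79 |
| 8 | 0.02 | 1.14 | 1.07 | 5.8% | 0.78 |
| 8 | 0.05 | 1.35 | 1.175 | 7.1% | 0.74 |
| 8 | 0.10 | 1.70 | 1.35 | 9.2% | 0.68 |
| 4 | 0.01 | 1.03 | 1.015 | 5.2% | 0.80 |
| 4 | 0.02 | 1.06 | 1.03 | 5.3% | 0.80 |
| 4 | 0.05 | 1.15 | 1.075 | 5.9% | 0.78 |
| 4 | 0.10 | 1.30 | 1.15 | 6.8% | 0.75 |

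**Step 5, check by simulation.** The planned ANCOVA was simulated under the null with 64 per arm and 40,000 replicates. With closed groups of eight it rejected in 5.3%, 5.9%, 7.4% and 9.0% of trials at ICC 0.01, 0.02, 0.05 and 0.10. With rolling entry (two entrants at every second session, each staying eight sessions) it rejected in 5.3%, 5.8%, 7.1% and 8.8%. Overlapping membership does not remove the problem.

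**Step 6, small-sample cost.** With groups of eight there are only 64/8 = 8 clusters. In a simulation with eight closed groups, d = 0.5 and no covariate, a partially nested test with Satterthwaite degrees of freedom held the type I error near 5%. Its power was about 0.74, 0.70 and 0.63 at ICC 0.02, 0.05 and 0.10, somewhat below the table.

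**The case against.** **Certainty.** A reader might infer that the type I error does exceed 5%. The document does not support that. It gives no ICC, and the excess arises only if the correlation that remains after baseline adjustment is positive. At 0.01 the excess is trivial. This stands, and the point is conditional.

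**Evidence for correlation.** A reader might take the protocol to name cohesion as an active ingredient. It does not. The Psychotherapeutic process section lists "group specific factors (cohesion and alliance with group members") among the scales of a session questionnaire, which is process measurement. The real support is the stated reason for the group size under Intervention development. That makes correlation plausible but does not show it.

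**Shared therapist.** The text speaks of a psychotherapist in the singular. If one person runs every group, the therapist effect is common to the whole arm. It then cannot be separated from treatment and creates no correlation within the arm. The therapist is therefore not part of the case.

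**Group size.** Eight is a ceiling. Enrolment began in September 2013 and was incomplete in May 2015. Assuming one weekly group without breaks over about 87 weeks, even all 64 patients × 8 sessions give 512/87 = 5.9 per session. Controls are also offered the program after follow-up and may take up places. The rows for four per group may thus be nearer the truth than those for eight. This stands.

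**Power.** A reader might infer that the stated 0.80 is simply too high. Since 128 results with or without a covariate, f = 0.25 could be on the unadjusted scale. With an assumed baseline correlation of 0.5, the residual variance is multiplied by 1 − 0.25 = 0.75. Power with groups of eight is then Φ(2.83/√(0.75V) − 1.96) = 0.88, 0.85 and 0.80 at ICC 0.02, 0.05 and 0.10. The power loss therefore depends on how f is read. The type I error does not.

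**Unseen analysis plan.** A cluster term could stand there, but the article states both the model and its covariates, and neither fits the delivery that it describes.

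**Conclusion.** The point holds in conditional form. The stated models and sample size assume independence, although one arm is treated in shared groups designed for interaction and the other is not. If outcomes correlate within therapy groups, the planned test is anti-conservative. The likely size runs from negligible (ICC 0.01 or small groups) to a true level of about 7% to 9% (ICC 0.05 to 0.10 with eight trial patients per group). Power falls below 0.80 over much of that range, provided that f = 0.25 is on the baseline-adjusted scale, and somewhat further with small-sample degrees of freedom. The same applies to the ANOVA fallback. The change should be made: it is cheap, and recruitment was still open at the time of writing, so the model can be fixed before analysis.

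**What to change.** In Statistical analyses, replace the ANCOVA, and likewise the ANOVA fallback, with a baseline-adjusted partially nested mixed model:

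- a random effect for therapy group in the intervention arm only;
- controls, and patients assigned to the intervention who never start, as singletons, so that the intention-to-treat set is kept;
- arm-specific residual variances and Satterthwaite degrees of freedom.

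Entry at every second session means that there are no discrete group cycles, and patients are randomized to condition, not to a group. Define the cluster either by entry cohort or by multiple membership, using the attendance that the therapist already documents (Acceptance of the treatment). Name one definition as primary and use the other as a sensitivity analysis.

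Report the estimated ICC with its uncertainty. In Sample size calculation, restate power as conditional on ICC (0.01 to 0.10) and group size, and say on which scale f = 0.25 is defined. More enrolment is not proposed.

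**Cost.** Some extra analysis work; wider intervals; an imprecise ICC from few clusters; a less favourable stated power; and a small loss if the ICC is in fact zero (power about 0.77 instead of 0.80 in the simulation with eight groups).
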